### Outcomes

#### Primary Outcome

The primary outcome of this study is to test the feasibility of the recruitment and intervention.

The intervention comprises a prolonged therapeutic fasting program combined with structured behavioral and educational support (medical supervision, group meetings, and online guidance).

Feasibility of recruitment will be evaluated by:

The number of patients screened and included within the 18-month recruitment period,The proportion of eligible patients who consent to participate, andThe time required to enroll a sufficient number of participants to start a group.

Feasibility of the intervention will be assessed by:

Treatment-related retention and dropout rates,Reasons for dropouts,Adherence to the fasting protocol on both the participants’ and therapists’ side.Adherence is monitored via the StudyU app, which records daily fasting compliance. Adherence is defined as completing at least 5 out of 7 fasting days while maintaining a caloric intake ≤350 kcal/day. If more than 30% of participants fail to meet this criterion, the intervention will be considered not feasible.

The StudyU app—an app to design and perform N-of-1 trials—is used to assess adherence daily. Adherence is defined as completing at least 5 out of 7 fasting days while maintaining a caloric intake of ≤350 kcal/day. If more than 30% of participants fail to meet this criterion, the intervention will be considered not feasible.

Feasibility of the assessments will be determined by:

The proportion of planned assessments that are completedThe duration of assessment visits, andThe number of dropouts due to assessment burden).

A completion rate of at least 75% is required to determine feasibility.

Acceptability of the intervention will be explored through:

Qualitative data from guided focus groups, andDropout reasons related to fasting burden.

Applicability of the measurement tools will be evaluated through completion rates, participant feedback, and data completeness for the validated questionnaires (NRS, VAS, BPI, FIQ, HAQ-DI, WHO-5, MAAS, BFI and PSQI).

Exploratory outcome for future trials:

With regard to a confirmatory study, an additional research question concerns the identification of a potential primary outcome parameter which validated questionnaire may best capture AIA/AIMSS symptom burden.

#### Secondary and Exploratory Outcomes

Four validated measurement instruments will be used to assess symptom burden at each study visit, see Figure 1 for illustration. Both the Numeric Rating Scale (NRS) and Visual Analog Scale (VAS) are widely recognized and validated measures of pain intensity. The Brief Pain Inventory (BPI) is used to assess the severity and location of pain, the effects of current medication or treatment, and its impact on mood.^
52
^ The Fibromyalgia Impact Questionnaire (FIQ) is a brief, self-administered, 10-item instrument designed to evaluate multiple dimensions of health status, including physical functioning, work status, depression, anxiety, sleep, pain, stiffness, fatigue, and overall well-being.^
53
^ Lastly, the Health Assessment Questionnaire-Disability Index (HAQ-DI) is a validated tool developed to measure the degree of difficulty adults with rheumatoid arthritis face in performing activities of daily life.^
54
^ Patients are also asked to list the 3 most bothersome symptoms and rate their severity on a 0 to 10 scale.

Even if a feasibility study lacks the power to detect efficacy effects, we have decided to integrate a number of questionnaires into the study in order to obtain a general tendency regarding possible effects that should be investigated in a confirmatory study. These questionnaires will be analyzed descriptively in order to evaluate, in the sense of exploratory testing, whether effects could be expected on average. Therefore, the following questionnaires are included at each study visit:

The World Health Organization’s 5-point index (WHO-5) is used to assess mental well-being,^
55
^ while mindfulness and awareness are measured using the Mindful Attention Awareness Scale (MAAS).^
56
^ The Brief Fatigue Inventory (BFI) is designed to assess cancer-related fatigue^57,44^ and the Pittsburgh Sleep Quality Index (PSQI) is used to measure subjective sleep quality.^
58
^

#### Additional Parameters

In order to describe the patient collective as accurately as possible, the following additional parameters will be recorded. At baseline sociodemographic data and medical history will be documented. Before starting the fasting intervention, participants are asked to report on their dietary habits by using a standardized questionnaire, please refer to Supplemental File 4. Besides dietary habits and the intake of stimulants, personal experiences with fasting as well as physical activity behavior are also recorded. Possible changes in dietary habits initiated by the fasting and nutritional counseling are documented at *t*2 (Supplemental File 4).

At each study visit (*t*0, *t*1 and *t*2) anthropometric data and adverse events are documented, and blood samples are offered on an optional basis. Anthropometric data include weight, height, BMI, heart rate, blood pressure, waist circumference and Bioelectrical impedance analysis (BIA) measurement. BIA will be used to assess for example, fat-free mass (FFM), skeletal muscle mass (SMM), total body water (TBW), intracellular and extracellular water (ICW/ECW), and phase angle (PA). To ensure reliable measurements, all assessments follow our institutional SOP, which includes standardized conditions such as: no food intake for at least 3 to 4 hours before measurement, adequate hydration the day before, avoidance of alcohol and caffeine for 24 hours and intense physical activity for 12 hours, and voiding the bladder immediately beforehand. Because the first BIA assessment occurs before the start of fasting and the second after the 3 day recovery period, these requirements can be met. The optional blood tests are collected primarily to provide participants with individualized feedback on metabolic and nutritional parameters at the end of the intervention. In addition, together with the anthropometric assessments, they serve as an additional evaluation of participants’ nutritional and general health status to ensure appropriate medical supervision and counseling before and during the fasting intervention. Blood biomarkers include fasting plasma glucose (FBG), gamma-GT, triglycerides (TG), high- and low-density lipoprotein-cholesterol (HDL, LDL), ferritin, CRP and insulin. Fatty liver index (FLI) and HOMA Index are calculated. The specimens are not stored for any further use.

In order to gain a better understanding of the individual experiences of the participants during the fasting process, they were asked to provide daily feedback in an N-of-1 trial app. Two questions will be posed daily via the StudyU app (VAS [Visual Analog Scale]; pain and fatigue), starting 1 week before, during and until 1 week after the intervention. This helps to assess the individual symptom burden. To evaluate the accompanying N-of-1 trials using the StudyU app, we aim to use a mixed methods approach, combining qualitative analysis of individual experiences with descriptive analysis of log report data.

After having completed their fasting intervention, up to 12 people will be conveniently sampled from the study cohort for a guided focus group (1 online session, lasting approx. 2 1⁄2 hours) to explore general acceptance as well as beneficial and inhibiting factors for the implementation of prolonged fasting. The German version of the semi-structured focus group guide is provided in Appendix (FREE-AI_Focus group guidelines). The discussion will be audio-recorded, transcribed verbatim, pseudonymized, and analyzed using a deductive-inductive content analysis approach. The deductive process of analysis will be guided by a socio-ecological framework introduced by Hull et al^
59
^ A similar approach was previously adopted in a qualitative study exploring the feasibility of a time-restricted eating intervention.^
60
^ A structured coding approach will be applied (2 coders will independently code qualitative data and discuss discrepancies) to identify key themes and patterns related to participants’ experiences, barriers, and facilitators of fasting adherence. Qualitative data will be managed using MAXQDA Software (Köln, Germany). (Supplemental File 5: Focus group guidelines)

### Sample Size and Statistical Analysis

The primary objective of the present study is its feasibility, assessed qualitatively and quantitatively as described in the methods section. Response rates and study compliance, as well as treatment adherence and dropout rates, will be calculated as the proportion of patients to whom a characteristic will be applied (eg, participation in follow-up measure) from the total population considered (all included patients) and will be reported as a percentage with corresponding 95% confidence interval (95% CI). Reasons for individual days of absence or study dropout will be reported qualitatively and quantitatively.

Descriptive statistics will be used to report baseline characteristics, including sociodemographic data and to evaluate possible effects that should be investigated in a confirmatory study. Given that this is a feasibility study, no statistical hypothesis testing or regression models will be applied, as the study is not powered to detect statistically significant effects. In order to inform the planning of a future confirmatory trial, we will obtain intervention effect estimates that is, assess whether pain and fatigue scores differ between intervention and non-intervention periods, both at the individual level and aggregated across participants. These analyses are exploratory, will estimate immediate average effects of applying the fasting intervention and are based on the assumption that the effects of fasting can be seen already within a few days. To this aim, we will apply linear regression models and Bayesian linear regression models, each with the pain and fatigue outcome variable assessed daily through the StudyU app, and an intervention indicator variable (*T*0 vs *T*1 and vs *T*2, respectively) as predictor. From linear regression models, we will obtain parameter estimates of mean differences between *T*0 and *T*1, and *T*0 and *T*2, and their standard error estimates, and from the Bayesian regression models we will obtain estimates of the posterior distribution of the treatment effects. These models will be fitted for each participant separately, and also together across participants. Together, both will give information about the size and variation of intervention effects. As further exploratory analyses, we will include linear time trends in the models, and the results may allow to generate hypotheses on possible underlying mechanisms. We will test assumptions of parametric models such as normality of residuals.

As this is a feasibility study, no formal power calculation was required for the primary objective. The target sample size of 54 participants was determined based on practical feasibility considerations, including recruitment capacity and an anticipated dropout rate of 10%. The sample size was chosen with uncertainty regarding the expected effect size in the confirmatory study. Since one of the objectives of the pilot study was to determine the appropriate primary endpoint for the main study, it was not yet possible to determine the effect size for the main study, which meant that its required sample size could not be adequately determined. As a result, we had to resort to rules of thumb for the pilot study’s sample size. Depending on the approach, these rules of thump range from 20 to 70 patients for a 2-arm randomized pilot trial. Whitehead et al (2016) evaluated these rules mathematically and showed that, even under conservative assumptions and very small expected effect sizes in the subsequent main trial, a 2-arm pilot study with approximately 50 participants provides adequate precision at 80% power (or about 75 participants at 90% power). Given that our study follows a single-arm pilot design a target sample size of 54 patients (including anticipated dropouts) can be considered conservative. The assumed 10% dropout rate reflects expected fasting-related discontinuation observed in previous fasting studies, while higher overall dropout rates reported in other studies were largely attributable to ongoing chemotherapy rather than fasting-specific tolerability.^
61
^

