#### Participant Timeline

The first participants were recruited in November 2023. It is planned to enroll 54 participants who will visit their respective study centers for 3 study visits: at baseline (*t*0), after completion of the 12-day fasting program, including 2 preparation days, 7 fasting days and 3 refeeding days (*t*1), (*t*1), and after 3 months (*t*2; see Figure 1 for illustration). The duration per patient is 12 weeks. Following the screening at baseline *t*0, all patients receive the intervention (prolonged therapeutic fasting program including structured behavioral and educational support).

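### The daily-app regressions are coded by T0/T1/T2, which the article defines only as study visits: as labelled, T0–T2 has no app data at 3 months and T1 falls after the fast

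*Protocol article*

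**What the plan says.** The Sample Size and Statistical Analysis section plans linear and Bayesian linear regressions, "each with the pain and fatigue outcome variable assessed daily through the StudyU app", with "an intervention indicator variable (*T*0 vs *T*1 and vs *T*2, respectively) as predictor". It promises mean differences for T0 against T1 and for T0 against T2, per participant and across participants. The stated aim is to "assess whether pain and fatigue scores differ between intervention and non-intervention periods" and to estimate the short-term mean effect of fasting, assuming that it shows within a few days.

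The time labels are defined under Participant Timeline, and only as visits: t0 at baseline; t1 "after completion of the 12-day fasting program, including 2 preparation days, 7 fasting days and 3 refeeding days"; and t2 at 3 months. The Additional Parameters section uses the same three labels for study visits. It also sets the app window for the two daily questions: "starting 1 week before, during and until 1 week after the intervention".

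The Interventions section calls the intervention a 7-day programme. It then says that the intervention also contains a preparatory phase and a gradual refeeding period.

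**The concern.** The outcome and the predictor belong to different time scales. The outcome is a daily series around the fast. The predictor, as far as the article defines it, is a set of three visits, the last at about 3 months. A model that combines them either has no outcome data for one of its promised contrasts or uses labels in a sense that the article never gives.

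The models are meant to show the size and variation of the effect for planning the confirmatory trial. If T1 contains no fasting day, or holds an unstated mix of preparation, fasting and refeeding days, the figure carried forward is not the short-term fasting effect it is said to be.

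**Working it through.** The article gives no figure for this point that could be reproduced, so the check is a day count. Day 1 is the first preparation day.

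**Inputs**
- Programme: 2 preparation + 7 fasting + 3 refeeding = 12 days (Participant Timeline). Preparation is days 1–2, fasting days 3–9, refeeding days 10–12.
- App window: 7 days before, the intervention, 7 days after (Additional Parameters).
- Length of the intervention: 7 days (Interventions) or 12 days (Participant Timeline).
- t2: 3 months, with a stated duration of 12 weeks per patient (Participant Timeline). I used 84 days (12 weeks) and 91 days (my assumption for 3 months), each counted from day 1 and from the end of the programme on day 12.

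**Step 1: last app day**
- 12-day intervention: 12 + 7 = day 19; 7 + 12 + 7 = 26 app days.
- 7-day intervention (days 3–9): 9 + 7 = day 16; 7 + 7 + 7 = 21 app days.

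**Step 2: gap from the last app entry to t2**

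| t2 placed at | Day | Gap, 12-day reading | Gap, 7-day reading |
|---|---|---|---|
| 84 days from start | 84 | 84 − 19 = 65 | 84 − 16 = 68 |
| 91 days from start | 91 | 91 − 19 = 72 | 91 − 16 = 75 |
| 84 days from day 12 | 96 | 96 − 19 = 77 | 96 − 16 = 80 |
| 91 days from day 12 | 103 | 103 − 19 = 84 | 103 − 16 = 87 |

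The gap is 65 to 87 days, so there are no app observations at t2. If the 12 weeks run from a baseline visit L days before day 1, the smallest gap becomes 65 − L. It would close only with a lead of 65 days, and the article gives no such lead.

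**Step 3: what T1 captures as a visit**
The t1 visit follows refeeding, so it falls after day 12. The fasting days are days 3–9. No fasting day belongs to T1 under this label.

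**Step 4: the phase reading (T0 before, T1 during, T2 after)**
- 12-day during phase: (2 + 3)/12 = 5/12 = 42% of its days are not fasting days.
- 7-day during phase: the before week is days −4 to 2 and holds 2/7 = 29% preparation days; the after week is days 10–16 and holds 3/7 = 43% refeeding days.

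As an illustration of the 12-day case, take a constant effect on the affected days, none on the other programme days, and equal weight per day. An effect confined to fasting days would then be estimated at 7/12 = 58% of its size. One lasting through refeeding would be estimated at (7 + 3)/12 = 83%. The article does not give the coding or the effect pattern, so neither figure is a prediction.

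**The case against.** The best reply is that T0, T1 and T2 were meant as the app phases before, during and after. The wording supports this. The predictor is called an intervention indicator, the aim compares periods, the effect sought is short-term, the app window has exactly three parts, and this section writes an upper-case T where the visits have a lower-case t. On that reading both contrasts have data, and T2 against T0 is a persistence contrast for the week after. A reader might therefore infer from the label problem that T0–T2 can never be estimated. The documents do not support that stronger statement: it has no data at 3 months, but it would have data for the week after if the labels meant phases. The reply does not dispose of the point, because the article nowhere defines the labels that way and the extent of the during phase remains open.

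It can also be said that the Interventions section counts preparation and refeeding as part of the intervention, so that 12 days is the natural reading and the before and after weeks are clean. That is fair, and it would remove the 2/7 and 3/7 shares. The 5/12 share would then apply. A whole-programme contrast is a legitimate target, but it is not the effect of the fasting days alone, and the plan should say which one it reports.

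Two further inferences go too far. One is that the contrast would be halved if an effect persisted into the after week. That requires pooling the before and after weeks, whereas the plan specifies T0 against T1 and T0 against T2 separately. The other is that symptoms from stopping stimulants during preparation would create a spurious improvement of a given size. The documents give no figure for such a rise.

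A detailed day-to-phase coding may well sit in a full analysis plan that is not shown. The finding does not rest on its absence. It rests on an outcome, a predictor and a collection window that the article itself states and that do not fit together.

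**Conclusion.** The point holds at moderate severity. With the labels as the article defines them, T0–T2 has no app data at 3 months, whether the intervention is read as 7 or 12 days, and T1 lies after the fast. With the undeclared phase reading, both contrasts can be estimated, but what T1 measures depends on an intervention length that the article gives in two ways. The shares of 5/12, or of 2/7 and 3/7, each hold under one of those readings and not both.

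A reader might infer that the trial's main conclusion is at risk. It is not. The section calls these analyses exploratory, the feasibility criteria do not use the app pain and fatigue scores, and the target of 54 does not rest on these models. What is at stake is the effect estimate handed to the confirmatory trial.

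**What to change.** In the app models, replace T0/T1/T2 with a phase factor derived from dates already recorded: before preparation, preparation (2 days), fasting (7 days), refeeding (3 days), after. Name fasting versus before as the immediate-effect contrast and after versus before as the persistence contrast. If a whole-programme contrast is also wanted, label it as such. Remove any 3-month contrast from the app models and report 3-month change only from the pain and fatigue questionnaires completed at the visits. State once whether the app window was timed to the 7 fasting days or to the 12-day programme.

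The cost is analysis wording and one derived variable. No new data are needed, and the diary start cannot be changed for participants already treated. The downside is fewer clean days if the diary was timed to the 7 fasting days: 7 − 2 = 5 before and 7 − 3 = 4 after per participant, instead of 7 and 7. The individual-level estimates would then be less precise.

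### The plan both rules out and specifies regression of the daily StudyU scores, and the regression as described makes no allowance for repeated days within a participant, so its standard errors are unreliable

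*Protocol article*

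**What the plan says.** All main statements are in the section Sample Size and Statistical Analysis of the protocol article.

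- Regression is excluded: "no statistical hypothesis testing or regression models will be applied, as the study is not powered to detect statistically significant effects".
- A few sentences later it is planned: "we will apply linear regression models and Bayesian linear regression models".
- The outcome is the daily score: "each with the pain and fatigue outcome variable assessed daily through the StudyU app".
- The main model has one named predictor: "an intervention indicator variable (*T*0 vs *T*1 and vs *T*2, respectively) as predictor". Linear time trends enter only as a further exploratory step.
- The outputs are mean differences between periods "and their standard error estimates", plus posterior distributions from the Bayesian fits.
- On the level of fitting: "These models will be fitted for each participant separately, and also together across participants". The two levels together are meant to describe how large the effects are and how much they vary, to help plan the confirmatory trial.
- On checks: "We will test assumptions of parametric models such as normality of residuals".

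The section Additional Parameters describes the same app data as receiving a mixed-methods evaluation whose quantitative part is descriptive. It also sets the diary window: one week before the intervention, the intervention itself, and one week after.

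**The concern.** There are two linked problems. First, the article gives incompatible instructions for one data set. One analyst would produce no model at all; another would produce effect estimates, standard errors and posteriors.

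Second, if the regression is run, the description fixes most of the model: the outcome, one predictor, the outputs and the two levels of fitting. A linear regression of that form uses a standard error that is valid only for independent observations. In the pooled fit, days from the same person share that person's usual level of pain and fatigue and that person's own response. In an individual fit, consecutive days are likely to resemble each other.

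At stake is the uncertainty attached to the diary effects. It is a named output and is meant to inform the next trial. The Data Collection section adds that the analysis of the intervention's effect is reported back to participants, so misjudged individual certainty would reach them too.

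**Working it through.** **No figure to reproduce.** The article states no standard error, SD or autocorrelation for the diary analysis. The sizes below therefore rest on assumed ranges.

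**Inputs from the article.** Diary blocks of 7 days before and 7 after (Additional Parameters). The middle block is 7 fasting days, or 12 days for the whole program (Participant Timeline). Days per person: 7 + 7 + 7 = 21, or 7 + 12 + 7 = 26. Participants: 54 with 10% dropout, 54 × 0.9 = 48.6, taken as 49. I read T0, T1 and T2 in the regression as the before, during and after blocks. That is my reading, because the timeline uses t2 for the 3-month visit.

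**Assumptions.** Within-person daily SD = 1; first-order autocorrelation ρ from 0 to 0.7; between-person SD 0, 1 or 1.5; SD of person-specific effects 0, 0.5 or 1. All SDs are in units of the within-person SD.

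**Individual fit, worked for ρ = 0.5 and blocks of 7.**
- Variance of a 7-day mean: v = (1/49)[7 + 2Σ(7−k)ρᵏ], k = 1 to 6, = (7 + 10.031)/49 = 0.3476.
- Covariance of adjacent block means: c = 0.0402.
- True variance of T1 − T0: 2(v − c) = 0.6148; true SE 0.784.
- Expected residual variance in the regression: 21(1 − v)/18 = 0.7612. Nominal variance: 0.7612 × 2/7 = 0.2175; nominal SE 0.466.
- Ratio true/nominal: 0.784/0.466 = 1.68.

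Ratios over both contrasts and both block lengths, with simulated coverage of a nominal 95% interval (40,000 series):

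| ρ | true SE / nominal SE | coverage |
|---|---|---|
| 0 | 1.00 | 95% |
| 0.2 | 1.21–1.23 | about 90% |
| 0.3 | 1.34–1.38 | 85–86% |
| 0.5 | 1.68–1.79 | 74–77% |
| 0.7 | 2.19–2.51 | 57–64% |

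**Pooled fit, 49 participants, no participant term.** The nominal variance uses the total residual variance s² and counts each day as separate: s² × 2/(49 × 7). The true variance is (effect variance + within-person contrast variance)/49, because a person's overall level cancels from the contrast.

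- *Too large.* ρ = 0, between-person SD 1.5, no effect variation: s² = 1 + 2.25 = 3.25. Nominal SE √(3.25 × 2/343) = 0.138; true SE √(2/343) = 0.076. Ratio about 0.56, coverage about 100%.
- *Too small.* ρ = 0.5, between-person SD 1, effect SD 0.5, blocks of 7, T1 − T0: s² ≈ 1 + 1 + (2/3)(0.25) = 2.167. Nominal SE √(2.167 × 2/343) = 0.112; true SE √((0.25 + 0.6148)/49) = 0.133. Ratio about 1.19, coverage about 90%.
- *Extreme.* ρ = 0.7, between-person SD 0, effect SD 1, 12-day middle block: ratio 2.11, coverage 65%.

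The full range is 0.56 to 2.11. Dropping the unrealistic case of no between-person variation leaves 0.56 to 1.68.

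**Spread of separate individual estimates.** With a daily SD of 1.2, ρ = 0.5 and identical true effects, the estimates still have SD 1.2 × 0.784 = 0.94. With a true effect SD of 1.0 they show √(1 + 0.885) = 1.37.

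**The case against.** The strongest reply is that the article does not say that days are treated as independent. It names a predictor and is silent on random effects and residual covariance, details that a condensed article may leave to an analysis plan. That stands as a limit: a reader might infer that the sponsor has chosen an independence model, and the text does not establish this. It does not remove the point. The contradiction about regression is in the text itself, and the model that is described yields the wrong standard error if followed.

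Other stronger readings also fail.

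- A reader might infer that independence will go unchecked. The sentence on assumptions gives normality only as an example and does not exclude other checks.
- A reader might infer that the raw spread of individual estimates will be taken as true variation in response. The text says only that both levels of fitting together inform on variation, and individual standard errors and posteriors are planned as well. The 0.94 above is a caution about that use, not an error in the plan.
- A reader might infer that pooled standard errors are too small. The ratio lies on both sides of 1, so no direction can be claimed.
- A reader might infer that the estimated effects are biased by this. In the set-up checked, with complete blocks, the mean differences are unbiased for the simulated effects; only their uncertainty is at issue.

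It is also fair that 95% intervals are not explicitly planned for these models, so coverage serves only as a measure of how far the standard errors mislead. Finally, the analysis is labelled exploratory, and the feasibility rules under Primary Outcome (adherence, and completion of assessments) do not use it. That lowers the severity, but it does not excuse an incorrect standard error when the standard error is itself a planned output.

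**Conclusion.** The point holds in limited form and should be fixed; it is not critical to the trial. The contradiction about regression is certain and needs no assumption. The standard-error problem follows from the model as described.

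- **Pooled fit:** generally wrong, in a direction that depends on between-person differences (which make the nominal value too large) and on autocorrelation and varying effects (which make it too small).
- **Individual fits:** wrong only if daily scores are autocorrelated, which is plausible but not documented.

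The sizes rest wholly on the assumed correlations and SDs. The consequence is confined to the precision and apparent variability of exploratory diary effects handed to the confirmatory trial.

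**What to change.** 1. Narrow the exclusion to confirmatory hypothesis testing, and align the description of the app data under Additional Parameters with the planned models.
2. For the pooled analysis, specify a linear mixed model, or its Bayesian hierarchical counterpart, with period effects, participant intercepts, participant-specific period effects and autocorrelated residuals. For the mean effect alone, participant fixed effects with cluster-robust standard errors would also serve.
3. Take variation in effect from the random-effect SD.
4. Report individual effects as partially pooled estimates from that model. Separate first-order autoregressive fits are only a partial remedy on so few days. In a simulation of 21-day series (6,000 per setting), coverage for ordinary regression against the autoregressive fit was 95% v 92% at ρ = 0, 86% v 89% at 0.3, 77% v 88% at 0.5, and 65% v 88% at 0.7.
5. Check residual autocorrelation as well as normality.

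The cost is a few lines of text and slightly more modelling work, with no new data.
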